# The connecting adolescents to reduce relapse (CARR) trial: study protocol for a randomized controlled trial comparing the efficacy of Groups 4 Health and cognitive behaviour therapy in young people

**DOI:** 10.1186/s12889-019-7011-y

**Published:** 2019-06-20

**Keywords:** Social isolation, Loneliness, Group psychotherapy, Mood disorders, Depression, Mental health, Adolescence, Youth, Social identity

## Abstract

**Background:**

Depression is the leading cause of disability in young people (aged 15–25) globally. Loneliness is a major factor in the development and relapse of depression in young people, yet few interventions directly address loneliness. Groups 4 Health (G4H) – a novel, theoretically derived group psychotherapy intervention – may address this disconnect. Previous trials (Phase I and Phase II) have found G4H to be efficacious in reducing symptoms of depression. However, the efficacy of G4H compared to current evidence-based treatments (Phase III) has not been investigated. This protocol details the design and methodology of the Connecting Adolescents to Reduce Relapse (CARR) trial, a randomised control trial assessing the efficacy of G4H in young people relative to cognitive behavioural therapy (CBT).

**Methods:**

The CARR trial is a two-arm non-inferiority randomised controlled trial that will compare the efficacy of G4H to the most widely used evidence-based treatment for depression, CBT, at program completion and 6- and 12-month follow up. Participants will be 200 young people (aged 15–25) with symptoms of depression and/or loneliness recruited from community and university mental health services. We hypothesise that the interventions will be comparable in reducing depression symptoms, but that G4H will be superior in reducing loneliness. Because loneliness is a primary risk factor for depression relapse in young people, we therefore expect the benefits of Groups 4 Health to be particularly apparent at 12-month follow up.

**Discussion:**

This trial will be the first to evaluate an intervention that targets loneliness, in comparison to the current gold standard treatment approach – CBT. If found to be effective, this program offers a new approach to treatment and relapse prevention of depression among young people.

**Trial registration:**

Trial prospectively registered on ANZCTR (ACTRN12618000440224), registered on 27/03/2018.

**Electronic supplementary material:**

The online version of this article (10.1186/s12889-019-7011-y) contains supplementary material, which is available to authorized users.

## Background

Depression has been ranked as the single greatest cause of disability in young people aged 15–25 [1]. Although both pharmacological and psychotherapy treatments are effective in reducing acute symptoms in young people [2], they come with a range of downsides. The cost of these treatments can be prohibitive [3], particularly because depression is more prevalent among disadvantaged communities [4]. There is also a global shortfall of mental health professionals who have the level of training required to provide these evidence-based treatments. This shortfall is most apparent in areas of greatest need, such as in non-urban areas with high rates of socioeconomic deprivation [5].

There are other barriers to the effective treatment of depression, particularly for young people. Previous research suggests that only a minority of young people with depression speak to a health professional about it [6], and only a minority of those who do receive best-practice treatment [2]. For instance, a common pathway to treatment is antidepressant medication prescribed following a consultation with a General Practitioner. However, the most common antidepressants prescribed for adults are not suitable for young people due to elevated suicide risk [7]. Even for those medications that are safe for adolescents, compliance rates are as low as 45% [8], often attributed to side effects such as weight gain and drowsiness. While most young people prefer non-drug treatment [9], the stigma associated with therapy often leads to treatment avoidance [10]. For these reasons, there is a need to develop treatment alternatives for young people with depression that are cost-effective, non-stigmatising, and widely accessible.

Furthermore, although short-term treatments are generally effective at alleviating acute symptoms, existing approaches to relapse prevention are only minimally effective. About 80% of individuals who have experienced a depressive episode relapse, experiencing an average of four episodes across a lifetime [11]. Even among those who receive best practice treatment, approximately one-third relapse within 18 months [12]. Therefore, new innovations in treatment should prioritise reducing depression recurrence.

### Loneliness as a promising target for intervention

Research has demonstrated that loneliness both precipitates and maintains depression. Longitudinal studies have shown that loneliness is a powerful predictor of depression onset, even after controlling for other candidate variables [13]. Loneliness also predicts poorer outcomes in depression treatment [14] and increases the risk of relapse [15]. These findings suggest that targeting loneliness may offer an effective approach to preventing relapse. Research has shown that when a person with depression joins a group, they reduce their risk of relapse four years later by approximately 24% [16].

Several diverse approaches to targeting loneliness have been developed [17]. These approaches mostly fall into two broad categories: either (1) *befriending* interventions, which seek to increase opportunities for social contact or provide social support, or (2) *cognitive* interventions which seek to address maladaptive cognitions or inadequate social skills. However, most of these interventions are not informed by theory, and evidence of their effectiveness is mixed [18, 19]. Indeed, Masi and colleagues stated that “﻿loneliness interventions to date have not attained the degree of efficacy achieved by interventions targeting other social and behavioural outcomes” ([19], p.257). Furthermore, loneliness interventions have, by and large, been developed and evaluated for older adults, with little attention paid to young people. Given the evidence that adolescents and young adults report some of the highest levels of loneliness in the population [20], there is particular need for research in this area.

### Groups 4 health

Groups 4 Health (G4H) was developed to fill this void as a theory-driven, group psychotherapy intervention that targets loneliness [21, 22]. G4H is informed by the Social Identity Approach to Health (see [23, 24] for a summary), which is a conceptual framework that articulates how social group memberships, and the social identities associated with them, affect health and wellbeing.

To date, two trials of G4H have been completed. The first was a Phase I pilot [25], in which the program was delivered to 81 people (*M*_age_ = 20.95; *SD* = 5.05) presenting with loneliness and affective disturbance (symptoms of depression or anxiety), of whom 54 completed G4H, and 26 completed the 6-month follow up. This group was compared to a matched, but not randomised, assessment-only control group. G4H was found to significantly improve mental health (depression, general anxiety, social anxiety, and stress), well-being (self-esteem, life satisfaction) and social connectedness (loneliness, social functioning), both on program completion and at 6-month follow up. Moreover, G4H recipients had significantly better outcomes than those in the control group at the 6-month follow up on measures of depression, anxiety, stress and self-esteem. In line with the theorised mechanisms of the G4H intervention, analyses also showed that participants whose identification with their G4H group and their subjective sense of belonging to multiple groups increased were most likely to experience improvements in depression, anxiety, stress, loneliness, and life satisfaction.

The second trial was a Phase II randomised control trial (RCT; [23]) in a sample of adults recruited from the community (*M*_age_ = 31.06; *SD* = 12.80). This RCT examined the efficacy of G4H compared to a Treatment-As-Usual (TAU) control among people with current depression symptoms or health-professional diagnosis of a mental illness (*N* = 120). In this trial, the TAU group received a diverse range of interventions, with more than 50% receiving antidepressant medication, psychotherapy, or both. Intention-to-treat analyses showed that people in the G4H condition experienced a significant decline in loneliness, social anxiety and primary care attendance, and a significant increase in their sense of belonging to multiple groups, relative to TAU. There was also evidence of significant pre-post improvement in depression among those who completed G4H, although this was not significantly greater than the improvement seen in the TAU condition.

These data suggest that G4H has good potential to benefit the mental health of young people in treatment. The next important stage is to test G4H against a *uniform, active treatment.* This is the purpose of the present program of research with young adults with depression.

### Aims

The project aims to evaluate G4H in comparison to the current gold standard evidence-based psychological treatment for youth depression, CBT. Based on the existing evidence, we predict:*Hypothesis 1:* At program completion, G4H will be superior to CBT in reducing loneliness (a major risk factor for relapse in depression).*Hypothesis 2:* At program completion, G4H will be as effective as CBT in reducing symptoms of depression (i.e., be non-inferior)*Hypothesis 3:* The benefits of G4H for loneliness and depression will be sustained at 12-month follow up.

## Method

### Trial design

CARR is a two-arm non-inferiority parallel (1:1 ratio) randomised controlled trial. A summary of this study’s compliance with Standard Protocol Items: Recommendations for Interventional Trials (SPIRIT), is provided in the Additional file 1.

### Participants

Participants will be 200 young people presenting with psychological distress recruited from two sources in South East Queensland, Australia: (1) a community youth mental health service (headspace, five sites), and (2) a university psychology clinic (University of Queensland). The following criteria will be used in recruitment:

#### Inclusion

Aged between 15 to 25 yearsEnglish speakingThe presence of depressive symptoms on the PHQ-9 (> = 5; corresponding to at least the mildly impairing clinical range; [23]);ORa health-professional diagnosed mental health condition (e.g., major depressive disorder);ORThe presence of elevated loneliness on the UCLA (> = 40; approximately 1 SD above the mean for adolescents; [26]).

#### Exclusion

Currently in receipt of other evidence-based treatment for depression (psychotherapy or psychopharmacology)Current high risk suicidal ideation or severe self-harming behaviour.Current psychotic episode or severe personality disorder that would interfere with ability to participate in group work.Severe neurological condition or severe learning impairment that would hinder engagement with the content of the proposed interventionsCurrent alcohol or other substance dependence / intoxication

Participants will be monitored throughout the trial for any change in these inclusion and exclusion criteria (e.g., in adjunct treatment status, or in suicide risk). Participants whose mental health declines for any reason will be provided with additional one-on-one supportive counselling by their group facilitator and referred to additional treatment where indicated. If a person who is initially eligible for the trial subsequently meets an exclusion criterion at any point during the active-treatment phase of the trial (T0-T5) they will be excluded from per-protocol analyses, but not intention-to-treat analyses.

### Recruitment

Allied health professionals and professionals-in-training at the two services will be invited to participate in an information session, which will include selection criteria for the participants, and a flyer for them to display within the service to inform participants of the program. These professionals will identify eligible patients for inclusion into the study on a rolling basis. They will approach potential participants and provide them with contact details for trial staff, including a website with links to the Participant Information Sheet and Consent Form. Research staff will contact potential participants to conduct screening and assessment, explain the study in more detail, answer any questions arising, and go through the consent process. If a potential participant indicates thoughts of self-harm in the baseline measures (i.e., a score of 3 or 4 on item 9 of the PHQ-9), a risk assessment will be conducted at this stage. Participants will provide fully informed, written and voluntary consent. Additionally, for those participants aged 16 or under, their parent or guardian will be informed of their participation and provided with an information sheet with the permission of the young person. However, primacy will be given to the consent of the young person, in line with the organisational policies of the research setting (which does not require parental consent for young people to access mental health services). Participants will be eligible to complete the CARR trial either as an (evidence-based) alternative to standard care, or while they are on a waiting list for standard care.

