### Intervention

Participants will be randomly assigned to receive either G4H or CBT. Groups will not commence unless a minimum of 5 people have consented to participate, with the maximum number of people recruited to each group being 9 people. Interventions are matched for contact time and mode of delivery, and both include five group sessions of 60–90 min in duration, run weekly for the first four weeks, and a final “booster” session that is held one month later. Postgraduate students in professional psychology (with provisional registration) will facilitate the groups (2 facilitators per group). Treatment fidelity and consistency of program delivery will be maintained by providing: a half-day of training, weekly group supervision from a registered clinical psychologist, direct observation by investigators to ensure quality, and regular team meetings with the research team. Additionally, G4H facilitators will anonymously complete a brief questionnaire at the end of each session to assess (a) what session activities were covered, (b) the length of session, and (c) facilitator session satisfaction and ease of delivery. Facilitators will also record participant attendance.

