### Measures

Each participant will be asked to complete online surveys (or paper-and-pencil if they prefer) at eight time points. The full questionnaire package measuring all outcomes of interest will be administered before the intervention (T0), on its completion (T5), 6 months later (T6) and 12 months later (T7) – see Table 1 for a summary. These should take about 10–20 min on each occasion. In addition, a brief one-page questionnaire will be administered at the end of each session (T1, T2, T3, and T4), which will (only) include measures of depression symptoms, loneliness, module feedback, and group identification.

**Table 1 Tab1:** Overview of CARR measures and timepoints of measurement

Construct	Measure	T0 Baseline	T1 After session 1	T2 After session 2	T3 After session 3	T4 After session 4	T5 Post-treatment	T6 6-month follow up	T7 12-month follow up
Primary outcomes	Depression (DASS-21)	•	•	•	•	•	•	•	•
	Depression (PHQ-9)	•					•	•	•
	Loneliness (4 item)	•	•	•	•	•	•	•	•
	Loneliness (20 item)	•					•	•	•
Secondary outcomes	Social anxiety	•					•	•	•
	GP attendance (last month)	•					•	•	•
	Wellbeing	•					•	•	•
	Life satisfaction	•					•	•	•
	Self esteem	•					•	•	•
	Subjective physical health	•					•	•	•
Process measures	Multiple group membership	•					•	•	•
	Multiple group compatibility	•					•	•	•
	Mental illness identity	•					•	•	•
	Group cohesion						•		
	Therapy group identification		•	•	•	•	•		
	Service identification						•		
Acceptability/feasibility	Useful		•	•	•	•	•	•	•
	Enjoyed						•	•	•
	Interesting						•	•	•
	Learnt something						•	•	•
	Homework completion		•	•	•	•	•		
	Facilitator questionnaire		•	•	•	•	•		
	Attendance		•	•	•	•	•		

Notes: *DASS21* Depression Anxiety Stress Scales (21 item)

*PHQ-9* Patient Health Questionnaire (9 item).

*GP* General Practitioner

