### Primary outcomes

*Depression, Anxiety and Stress Scale* [30]*.* This measure comprises 21 items, 7 for each construct, for example “I felt that life was meaningless”, rated on a 4-point scale (0 = did not apply to me at all, 3 = applied to me very much, or most of the time. It has been validated for use with adolescents as young as 11 years in Australia [31], with an improvement greater than 3 points considered clinically significant [32]. The full DASS-21 (including anxiety and stress subscales) will be administered at T0, T5, T6 and T7, while the depression subscale will be administered at all timepoints T0-T7. The 9-item Patient Health Questionnaire is included as an additional measure of depression (T0, T5, T6, T7); this will be used as a screening tool rather than as the primary outcome measure.

*UCLA-20:* The UCLA Loneliness scale has been validated for use with a young adult sample [33, 34]. It comprises 20 items, for example “Felt isolated from others” requiring a response on a 4-point scale (1 = never, 4 = often). The full scale will be included at T0, T5, T6 and T7, and a 4-item version of the UCLA scale will be included in the end of session questionnaire (T1-T4).

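### The baseline self-harm trigger (3 or 4 on PHQ-9 item 9) leaves some answers that report such thoughts without a risk assessment, whichever item coding is assumed

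*Protocol article*

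**What the plan says.** In the Recruitment section, research staff carry out screening, assessment and consent. A risk assessment follows at that point if a potential participant "indicates thoughts of self-harm in the baseline measures (i.e., a score of 3 or 4 on item 9 of the PHQ-9"). The opening words say whom the step is for, and the parenthesis makes it concrete.

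Other parts of the article bear on this rule:

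- **Inclusion** uses a PHQ-9 total of 5 or more as one of three alternative routes into the trial. The article does not give the response options or scoring of the individual items.
- **Exclusion** lists "Current high risk suicidal ideation or severe self-harming behaviour", and adds that "Participants will be monitored throughout the trial for any change in these inclusion and exclusion criteria", with suicide risk named as an example.
- **Primary outcomes** fixes when the instrument is given: "The 9-item Patient Health Questionnaire is included as an additional measure of depression (T0, T5, T6, T7").
- **Measures** describes a one-page form after each of the first four sessions, "which will (only) include measures of depression symptoms, loneliness, module feedback, and group identification". Table 1 shows that the depression measure on that form is the DASS-21, not the PHQ-9.
- **Intervention** sets five sessions, "run weekly for the first four weeks", with a booster one month later.

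**The concern.** The sentence sets out a purpose (assess those who report thoughts of self-harm) and then equates it, by *i.e.*, with two scores. If those scores do not cover every answer that reports such thoughts, staff who follow the rule exactly, or a web survey programmed from it, will pass over people whom the opening words include.

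The baseline answer carries weight here. Participants are aged 15 to 25, may be on a waiting list for standard care, and are excluded if they already receive another evidence-based treatment for depression. This is the only numeric trigger for a baseline risk assessment that the article gives, and such an assessment informs the high-risk exclusion. The scheduled forms do not ask the same question again until the end of treatment.

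What is at stake is participant safety. No estimate, margin or power figure depends on it.

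**Working it through.** **Inputs.** Trigger set {3, 4} (Recruitment). PHQ-9 total cut-off of 5 or more (Inclusion). Nine items, given at T0, T5, T6 and T7 (Primary outcomes; Table 1). Session timing (Intervention). The coding of item 9 is not stated, so it is an assumption and is varied below. In each case exactly one option is taken to mean no such thoughts.

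**Step 1: which answers are missed.** For each coding, list every answer that reports thoughts of self-harm, then remove 3 and 4.

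| Assumed coding | Answers reporting thoughts | Of these, trigger | Not triggered | Share of options missed |
|---|---|---|---|---|
| 0-3 (0 = none) | 1, 2, 3 | 3 | 1, 2 | 2/3 |
| 1-4 (1 = none) | 2, 3, 4 | 3, 4 | 2 | 1/3 |
| 0-4 (0 = none) | 1, 2, 3, 4 | 3, 4 | 1, 2 | 2/4 |

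Two less likely codings give the same conclusion. Coded 1-5 (1 = none), answers 2 and 5 are missed (2/4). Coded 1-4 in reverse (4 = none), answers 1 and 2 are missed (2/3). At least one such answer is missed in all five. In the three tabulated codings the highest answer does trigger.

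The rule would be complete only if two or more options meant no such thoughts. Nothing in the article suggests that.

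**Step 2: which coding fits the rest of the article.** The lowest possible PHQ-9 total is 9 × the lowest item score.

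- Items coded from 0: 9 × 0 = 0, so a cut-off of 5 can screen people out.
- Items coded from 1: 9 × 1 = 9, so everyone reaches 5 and the criterion selects nobody.

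Unless totals are rescaled, the cut-off points to coding from 0. Both such codings above miss answers 1 and 2. With four options coded 0-3, a score of 4 does not exist and only the single highest answer triggers. On a four-option item, with no rescaling between item and total, the trigger of 3 or 4 and the cut-off of 5 cannot both work as intended.

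**Step 3: when item 9 is next asked.** Put session 1 at week 0. Sessions 2, 3 and 4 then fall at weeks 1, 2 and 3. The booster, where T5 is collected, comes about 4 weeks later: 3 + 4 = about week 7. Baseline precedes session 1, and a group does not start until at least 5 people are available, so the interval from T0 is 7 weeks plus any such wait.

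**Step 4: the check on the remedy.** With the trigger set to any answer above the lowest (1 or more if coded from 0, 2 or more if coded from 1), the missed set is empty for every coding in which the lowest score means no such thoughts.

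**The case against.** The best defence is that *i.e.* introduces an operational definition: for this step, indicating self-harm thoughts simply means scoring 3 or 4, and the word *any* appears nowhere. Where to place an automatic trigger is a clinical triage decision. If the survey stores items as 1-4, the rule picks out the top two answers, which is a coherent threshold, and a recoded total would be consistent with the cut-off of 5. The coding is not in the article, so neither the size of the gap nor the impossible score can be shown for certain.

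The defence can also point to safeguards that do not depend on item 9. Service professionals identify patients, and research staff screen each one. High-risk ideation is an exclusion for everyone. Suicide risk is monitored, with counselling and referral. Two facilitators see each group weekly for four sessions under clinical supervision, and the DASS-21 depression subscale is given at every timepoint. A fuller risk procedure may sit in the full protocol.

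Much of this stands. The other safeguards are real and lower the practical risk, and the option counts say nothing about how many people are affected. A higher threshold may have been intended.

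The defence does not rescue the rule as written. No severity threshold is stated, the opening words describe a wider group than the scores capture, and this holds under every coding tried. The criticism is directed at a rule that the article states, not at detail left to another document.

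**Conclusion.** The concern holds. Followed literally, the rule fails to assess some young people who report self-harm thoughts at baseline. It misses one third (coding 1-4) to two thirds (coding 0-3) of the answer options that report them. The PHQ-9 cut-off favours coding from 0, where answers 1 and 2 are both missed. The next scheduled item 9 is about 7 weeks after session 1, plus any wait for the group to form.

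This rests on two assumptions: the item coding, which the article does not state and which was varied, and that only one option means no such thoughts. The article gives no response frequencies, so the number of participants affected cannot be estimated.

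The fault is confined to one safety step and is not an absence of safeguards. It should be corrected on safety grounds. The non-inferiority margin, sample size and analysis are unaffected.

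**What to change.** Define the trigger by response, not by number: any item 9 answer above the lowest option prompts the risk assessment. State the coding next to the rule, so that this reads as 1 or more if coded 0-3 or 0-4, or 2 or more if coded 1-4. Then check that the rule in the web survey, and on any paper form, matches.

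If the clinical lead deliberately wants a higher threshold, describe it as frequent thoughts of self-harm and use only values that exist under the coding in use.

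The cost is a one-line correction, a check of the survey rule, and some additional brief risk assessments at screening. The assessment itself is already planned, so no new procedure is needed.
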